#### Task-Based Functional MRI: Visuospatial Corsi Blocks: Block Span Task

Participants will engage in a scanner-adapted visuospatial task programmed in EPrime, using a modification of the block span task (BS) [as per (81)] in the scanner.

#### Task Description

Instead of using blocks, the scanner will visually present 10 squares. Each square will correspond to 1 of 10 keys (one for each finger) on the response pad. The experiment will contain 24 visual sequence periods. A sequence consists of the presentation of *n* randomized stimuli. The stimuli will be a single yellow block presented for 2s. We will customize the sequence length by adding one stimulus to baseline performance (*n* = BS + 1) collected outside the scanner before scanning. We will instruct participants to remember the location of the yellow squares as they appear, with no button press during this visual sequence period. At visual sequence period end, the participants will recall the sequence by pressing fingers on the response pad in the same order as the previously presented squares. The recall phase lasts 11s. Between two visual sequences, we will present an interstimulus interval (ISI) with jittered duration between 1.5 and 3.5s. Participants will perform the BS until they have two recall failures at the same span length. Before scanning, all patients will learn the pairing of each visual stimulus with the appropriate button response, using the less affected hand, and will practice until they are able to quickly and accurately match each stimulus with the appropriate response. We consider one sequence as correct when at least 70% of the spatial stimuli are recalled correctly to calculate patient correct response rate.

### Analyses

#### Aim 1

We will analyze the primary study outcome with a mixed effect model (treating subject as random) with between-subjects effect of group (PDAE vs. WALK) and within-subjects timepoints (study entry, 3-month follow-up, 16-month follow-up) plus their interaction term. If the interaction term is significant, we will test differences between PDAE and WALK in the change from baseline to 3 months and from baseline to 16 months using Holm's procedure to control for multiple testing. We will consider covariates sex and H&Y staging (<III, ≥III) in the analyses.

#### Aim 2

The secondary outcome Corsi Blocks Score will be analyzed using a similar mixed effects model.

#### Aim 3

We will use similar analyses. We will use mixed effects model except that it will be a two-group (PDAE vs. WALK) and a two-level variable for time (study entry vs. 16-month follow-up).

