### Power and Sample Size for the Primary Outcome

The trial is powered for the primary outcome, MDS UPDRS-IV total score. A differential effect size of *d* = 0.89 in the change of OFF-time for PDAE vs. walking using data collected by Uc et al. (30) was observed (Table 1) (30).

Given the study design's 3- and 16-month timepoints, we will use Holm's procedure (62) to control for multiple testing. The alpha levels will be 0.025 and 0.05 for *p*-values in ascending order for comparing PDAE and WALK in the changes from the baseline at 3 and 16 months. The observed effect size (*d* = 0.89) is from participants that finished their programs in the shorter duration pilot studies; therefore, we expect the intent-to-treat effect size will be reduced. Thus, we power the study for an attenuated effect of the observed effect: *d* = 0.7, which is 64% of the observed effect size in our pilot study or 79% of the estimated effect vs. walking, giving us 81 and 88% power for the comparisons at alpha level of 0.025 and 0.05, respectively. With a sample size of *n* = 41 completers per group, total *n* = 82, we additionally expect to have medium to high (60–80%) power to detect differences between the PDAE and WALK groups on the visuospatial outcome (Aim 2), given that the estimated effect size for Corsi Blocks is 0.76 vs. a cognitively engaging contact control (63). We will assume 25% attrition and will therefore recruit 102 participants with PD. For the exploratory variables, we will only focus on effect estimation instead of inference testing given that we do not know the effect size.

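### The primary analysis compares raw changes from baseline; using the baseline score to gain precision would raise power at no cost in patients

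*Protocol article*

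**What the plan says.** The Analyses section, Aim 1, states: "We will analyze the primary study outcome with a mixed effect model (treating subject as random) with between-subjects effect of group". The other factor is "within-subjects timepoints (study entry, 3-month follow-up, 16-month follow-up) plus their interaction term". The follow-up tests, which depend on that interaction, are given as: "we will test differences between PDAE and WALK in the change from baseline to 3 months and from baseline to 16 months". Multiplicity across the two visits is handled by Holm's method. On covariates it says only: "We will consider covariates sex and H&Y staging (<III, ≥III) in the analyses".

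Aim 2 (Corsi Blocks) uses a similar model. For Aim 3: "We will use mixed effects model except that it will be a two-group (PDAE vs. WALK) and a two-level variable for time", the two levels being study entry and 16 months.

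The power section works on the same basis. Its effect size comes from change scores (Table 1), "we power the study for an attenuated effect of the observed effect: *d* = 0.7", and "The alpha levels will be 0.025 and 0.05 for *p*-values in ascending order". It reports 81% and 88% power with 41 completers per group.

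**The concern.** Study entry is part of the response and group has a free effect at that visit. The tested contrast is therefore the follow-up difference minus the observed baseline difference. In a randomised trial the baseline means are equal in expectation, so subtracting the whole observed baseline difference adds noise unless baseline and follow-up are perfectly correlated. Adjusting for the baseline score, or constraining the two arms to a common baseline mean, removes that noise without introducing bias in large samples. Naming an unstructured covariance elsewhere would not by itself recover this precision, because the group effect at baseline stays free.

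The margin is thin. At alpha 0.025 the plan sits one point above 80% power, and it expects only 60–80% for Corsi.

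A second, conditional issue concerns the within-subject covariance. The only dependence named is a random subject effect. If that means a random intercept and nothing more, one common correlation is imposed on visits at 0, 3 and 16 months.

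**Working it through.** **1. The plan's own figure.** Inputs from the power section: d = 0.7 in SDs of change, 41 completers per group, alpha 0.025 and 0.05. Sidedness is not stated; two-sided is assumed. A two-sample t test on change scores (noncentral t, 80 df, noncentrality 0.7 × √(41/2)) gives 81.0% and 87.9%, against the stated 81% and 88%. One-sided tests (normal approximation) give 88.7% and 93.6% and do not match.

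**2. Gain with equal SDs.** Let s be the SD at each visit and ρ the baseline/follow-up correlation.
- Var(change) = 2s²(1 − ρ)
- Var(baseline-adjusted) = s²(1 − ρ²)
- Ratio = (1 + ρ)/2
- For the same raw effect, the standardised effect becomes 0.7/√((1 + ρ)/2)

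The article gives no ρ, so a range is assumed. Power is for 41 per arm with 79 df.

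| ρ | Variance ratio | Variance cut | Power, alpha 0.025 | Power, alpha 0.05 | Per arm for 81.0% at alpha 0.025 |
|---|---|---|---|---|---|
| 0.4 | 0.70 | 30% | 93.1% | 96.3% | 30 |
| 0.5 | 0.75 | 25% | 91.3% | 95.1% | 32 |
| 0.6 | 0.80 | 20% | 89.4% | 93.8% | 34 |
| 0.7 | 0.85 | 15% | 87.3% | 92.4% | 36 |

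**3. Effect of the entry criterion.** The Participants section requires a score of at least 1 on item 4.3, so the sample is partly selected on baseline. Assume normal scores, scaled to unit variance before selection, with the lowest part of the baseline distribution excluded. Selection on baseline leaves the slope b (equal to the unselected ρ) and the residual variance 1 − b² unchanged, but reduces the baseline variance to v. Then

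Var(adjusted)/Var(change) = (1 − b²) / [(1 − b²) + (1 − b)²v].

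- Lowest quarter excluded, v = 0.535. With b = 0.4: 0.84/(0.84 + 0.36 × 0.535) = 0.814, a 19% cut, power 88.8%. With b = 0.7: 0.51/(0.51 + 0.09 × 0.535) = 0.914, a 9% cut, power 84.6%.
- Lowest half excluded, v = 0.363. With b = 0.4: ratio 0.865, a 13% cut, power 86.7%. With b = 0.7: ratio 0.940, a 6% cut, power 83.5%.

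Power is at alpha 0.025 with d held at 0.7 SDs of change. Selection lowers the observed correlation, but it also shrinks the baseline variance, so the gain falls. The ratio (1 + ρ)/2 must not be applied to the lower observed correlation, because the SDs are then unequal.

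**4. Covariance, if the model is a random intercept only.** With complete data and unit variances, such a model uses one variance for both changes, 2 × (1 − mean of the three correlations). The true variance is 2 × (1 − correlation of that visit with baseline). The correlations below are assumptions, in the order baseline–3, baseline–16 and 3–16 months.

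| Correlations | Model SE/true SE, 3 mo | Model SE/true SE, 16 mo | Size of a nominal 5% test, 3 mo | Size, 16 mo | Any false rejection: Holm alone | With interaction gate |
|---|---|---|---|---|---|---|
| 0.5, 0.5, 0.5 | 1.00 | 1.00 | 5.1% | 5.1% | 4.8% | 3.7% |
| 0.6, 0.4, 0.5 | √(1.0/0.8) = 1.12 | √(1.0/1.2) = 0.91 | 2.8% | 7.4% | 4.8% | 3.8% |
| 0.7, 0.4, 0.5 | √(0.933/0.6) = 1.25 | √(0.933/1.2) = 0.88 | 1.6% | 8.3% | 5.2% | 4.2% |

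Test sizes are from 40,000 simulated null trials with 41 per arm.

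**The case against.** The strongest defence is that nothing here is invalid. The group difference in change is unbiased, matches the stated hypotheses, and has the power claimed for it at each alpha level. All of that stands, and it makes this a recommendation on efficiency. It does not remove the point: the contrast and the covariate list are stated choices, not details that a condensed article has left out.

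A second defence is that the covariance structure is commonly left to a fuller document. The article names no residual covariance and excludes none, and it cites PROC MIXED, which can fit an unstructured one. This also stands. A reader might infer that the plan forces equal correlations and therefore misstates its standard errors. The text does not establish that: it needs both a random-intercept-only reading and correlations that differ between visits, and the article reports no correlations. A reader might also take the 7–8% size of a single 16-month test as the trial's error rate. Under the planned procedure, in the cases simulated, the chance of any false rejection was 4.8–5.2% with Holm alone and 3.7–4.2% with the interaction gate. Error moves from 3 to 16 months; it does not clearly rise overall.

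Third, one might expect the OFF-time entry criterion to increase the benefit of adjustment through regression to the mean. Step 3 shows the reverse under the stated assumptions, so the equal-SD gains may be optimistic for this population.

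**Conclusion.** The plan gives up precision that its own baseline data could supply. The planned test is unbiased and its stated power is correct for the change-score comparisons as written.

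The size of the loss rests on assumptions, because the article reports no baseline/follow-up correlation. With correlation 0.4–0.7 and equal SDs, the variance falls by 15–30% and power at alpha 0.025 rises from 81% to 87–93%. If entry selection removes the lowest quarter to half of normal baseline scores, the variance cut is about 6–19% and power about 83–89%. The selection model is a proxy: entry is on one item, not on the total score.

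The covariance issue is secondary and conditional. If the model is a random intercept alone and correlation decays with time, the standard error would be too large at 3 months and too small at 16 months. It does not apply to Aim 3, where two time points have only one correlation.

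**What to change.** - **Aim 1:** fit a longitudinal model with a common baseline mean in both arms, or take 3 and 16 months as the responses with the baseline MDS-UPDRS-IV score (by time) as a covariate. In the same sentence, specify an unstructured within-subject covariance.
- **Interaction gate:** if baseline leaves the response, the group-by-time term alone tests only whether the effect differs between 3 and 16 months. The gate should then be restated as a joint test of no group difference at either follow-up visit, followed by Holm as planned.
- **Aim 2:** use the same form for Corsi.
- **Aim 3:** use ANCOVA of the 16-month iron (R2*) and SNc volume measures on their baseline values.

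The cost is a few lines in the analysis section. All baseline scores are already collected, so no visits, data or participants are added, and the sample size can stay as it is. The change should be fixed before any comparison by arm.

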## Study Design

### Overall Study Design

The PAIRED trial builds upon more than 10 years of research investigating unique motor, cognitive, and symptomatic benefits of PDAE. The study will perform a two arm, randomized controlled trial comparing efficacy of PDAE vs. WALK for improving OFF-time and visuospatial cognition among individuals with PD who report OFF-time. We will randomize *n* = 82 participants equally to 16 months of PDAE (*n* = 41) or to walking as aerobic exercise WALK (*n* = 41) in blocks of two to reduce variability within treatment conditions. Participants will be stratified by sex and Hoehn & Yahr (H&Y) staging (I, II, or III). The 16-month intervention period will consist of Training (3 months) and Maintenance (13 months) phases. In Training, participants will complete 20 biweekly 90-min sessions. In Maintenance, participants will complete 90-min weekly sessions. To evaluate SNc neurodegeneration over the observation period, we will image patients at study entry and 16-month follow-up using fMRI sequences. We will compare SNc volume and iron accumulation estimates in PDAE vs. WALK to assess whether PDAE is more neuroprotective.

Participants will be assessed at baseline, 3 months (immediately post-Training), and at 16 months (immediately post-Maintenance) for OFF-times, cognition, and neuroprotection, as evaluated in the SNc. At a standardized time of day, participants will be tested on all outcome measures at least 12 h after their last dose of antiparkinsonian medications. Furthermore, participants will keep an OFF-time diary to corroborate MDS-UPDRS-IV assessments. Participants will be ON medications during intervention. In addition to the primary motor and cognitive outcome measures, participants will be tested on secondary behavioral motor and cardiovascular and cognitive outcomes. Participants will undergo NM-MRI and fMRI scans at baseline and 3 and 16 months assessments to investigate mechanisms by which cognitive benefits have been obtained and replicated by PDAE and whether PDAE vs. WALK is neuroprotective, as exhibited by slowed rate of NM loss and iron accumulation and increased functional connectivity with spatial cognitive areas.

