## Participants

Informed consent will be obtained prior to randomization. To account for 25% attrition, we will recruit 102 participants with PD for this study. For group assignment, we will recruit PD patients (age ≥40, Hoehn & Yahr stage I–III) who report OFF-time, indicated by score ≥1 on UPDRS-IV item 4.3, i.e., time spent in the OFF-state. Their PD diagnosis (ICD-10 G20^*^) will be based on established criteria (64) and determined by a board-certified neurologist with training in movement disorders. Individuals must present asymmetric symptoms that include at least three of the cardinal signs of PD (rigidity, bradykinesia, tremor, postural instability) and must show clear symptomatic benefit from antiparkinsonian medications (65). Participants will be recruited from the Atlanta VA HCS Movement Disorders clinic and the Emory Movement Disorders clinic, as well as at local Parkinson-related support groups, educational meetings, and community events. We will also recruit via the Michael J. Fox Foundation FoxFinder web-based registry. Based on the ≈60% prevalence of reported OFF-times among participants in ongoing studies and our ability to recruit one in five contacted participants, we plan to initially contact 656 potential participants to reach the enrollment goal.

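### Randomisation is stratified by sex and three H&Y stages, but the analysis makes adjustment optional and pools stages I and II

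*Protocol article*

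**What the plan says.** Under Overall Study Design: "Participants will be stratified by sex and Hoehn & Yahr (H&Y) staging (I, II, or III"). Allocation is 1:1, "in blocks of two to reduce variability within treatment conditions". With two sexes and three stages there are six strata.

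Under Participants, entry is limited to the same range: "we will recruit PD patients (age ≥40, Hoehn & Yahr stage I–III) who report OFF-time".

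Under Analyses, the text for Aim 1 reads: "We will analyze the primary study outcome with a mixed effect model (treating subject as random) with between-subjects effect of group (PDAE vs. WALK"), with three time points and the group-by-time interaction. If the interaction is significant, the plan is to "test differences between PDAE and WALK in the change from baseline to 3 months and from baseline to 16 months using Holm's procedure". On covariates the section says: "We will consider covariates sex and H&Y staging (<III, ≥III) in the analyses". It does not explain the two-level grouping, or say whether the covariates enter as main effects or crossed with time. Aims 2 and 3 refer back to a similar model.

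**The concern.** Two features do not fit the design. First, the randomisation separates stage I from stage II and the analysis merges them. Second, the verb 'consider' leaves open whether sex and stage enter the primary model at all, so more than one primary analysis is compatible with the text.

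When allocation is balanced on a factor that predicts the outcome and the model omits it, the model-based standard error still contains variance that the design has removed from the comparison. The test is then somewhat conservative and the stratification brings no gain in the analysis. At stake are a little precision and an avoidable choice over the primary p-value. The validity of the treatment estimate is not at stake.

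**Working it through.** **1. The plan's own power.** Inputs from Power and Sample Size: d = 0.7, 41 completers per group, "The alpha levels will be 0.025 and 0.05 for *p*-values in ascending order". For a two-sided two-sample t test the noncentrality is 0.7 × √(41/2) = 3.17 with 80 df. Power is 81.0% at 0.025 and 87.9% at 0.05, matching the stated 81% and 88%. The stated power thus assumes no covariate adjustment and does not depend on how H&Y is coded.

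**2. Factors side by side.**

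| | Sex | H&Y levels | Status |
|---|---|---|---|
| Randomisation | yes | I / II / III | fixed |
| Analysis | yes | I+II / III (≥III can only be III) | optional |

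Sex and the III-versus-rest split are named in both places. Only the I-versus-II split is lost by the coding.

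**3. What a main effect does in the stated model.** Write Y(it) = u(i) + βX(i) + time + group × time + error, with X fixed over time. The change Y(it) − Y(i0) contains no βX(i), so with complete data a main-effect covariate drops out of the tested contrasts. Simulation of this mixed model (60 trials per scenario; assumed stage shares 15/60/25%; assumed 0.5 SD per stage on level) agrees:

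- Complete data: SE of the change contrast 0.2199 with no covariates, with collapsed H&Y and with three-level H&Y; estimates identical to five decimals.
- 25% missing at 16 months: mean SE 0.2220 for both collapsed and three-level H&Y.
- Covariates crossed with time, stage also shifting change by an assumed 0.5 SD per stage, complete data: 0.2261 unadjusted, 0.2220 collapsed, 0.2201 three-level. Three-level against collapsed: 0.2220/0.2201 = 1.009, about 0.9%.

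A gain appears only if stage predicts change and the terms are crossed with time, or change itself is modelled.

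**4. Adjusting versus not adjusting.** Let R² be the share of change variance explained by the strata (assumed 5–10%; the article gives none). In a change-score model the effective effect is 0.7/√(1 − R²):

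- R² = 0.05: 0.718, power 83.1% at alpha 0.025.
- R² = 0.10: 0.738, power 85.2%.

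This formula ignores imperfect balance. Simulated change-score trials (4,000 per scenario; six strata, blocks of two, 102 randomised, 82 analysed; stages 15/60/25% or even) gave 81–82% unadjusted and 82–85% adjusted, a gain of about 1–4 points. The unadjusted nominal 5% test had true size of about 4.2–4.6%.

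**5. Three levels versus two.** Assume the stage effect is linear.

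- Shares 15/60/25%: variance of stage = 4.80 − 2.10² = 0.39. The part within the pooled I+II group is 0.75 × 0.20 × 0.80 = 0.12, so pooling loses 0.12/0.39 = 31% of the explained variance.
- Even shares: (2/3 × 1/4)/(2/3) = 25%.

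The SE ratio is √(1 + lost/(1 − R²)):

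- Smallest case, even shares and R² = 0.05: √(1 + 0.0125/0.95) = 1.007.
- Largest case, 15/60/25% and R² = 0.10: √(1 + 0.0308/0.90) = 1.017.

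That is 0.7–1.7% before the cost of the extra degree of freedom. The simulations gave about 0.5–1.6%, or at most about 1 power point.

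**The case against.** The strongest defence has three parts.

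- **The stated model.** The primary contrasts are within-subject changes, so the coding of a time-invariant main effect hardly matters. This stands. It is why the size must be kept small and why adding main effects would not be enough.
- **Pooling can be sensible.** If few stage I patients report OFF-time, merging I with II is reasonable, and it neither biases the effect nor inflates type I error. This also stands, but the article gives no stage counts and no such reason.
- **Covariate detail belongs in an analysis plan that is not shown.** This stands in part. An article may leave the matter out, but this one states a covariate specification that departs from its own randomisation.

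A reader might go further and infer that pooling I and II costs 2–4 power points, or makes the confidence intervals materially too wide. The documents do not support that. Those figures compare full adjustment with none, in a change-score model, under an assumed R². The I-versus-II split alone carries only a quarter to a third of that assumed variance.

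**Conclusion.** The mismatch and the optional wording are certain from the text. Their consequence is modest: no bias, no inflation of type I error, a slightly conservative test if the strata are left out, and a small forgone gain.

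The sizes rest on assumptions that the article can neither confirm nor exclude: 5–10% of change variance explained by the strata, a linear stage effect, and stage shares of 15/60/25% or even. If stage is unrelated to change in MDS-UPDRS-IV, the loss is nil.

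The optional wording matters at least as much as the pooling. In the change-score simulations at d = 0.7 and alpha 0.025, the unadjusted and three-level analyses reached opposite conclusions in a few per cent of trials; collapsed and three-level coding did so in about 2%. A choice that can change the primary conclusion even that often should be settled before the data are seen.

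**What to change.** - Replace 'consider' with 'include', so that adjustment is definite.
- Use sex and H&Y at the three levels recorded at randomisation. Alternatively, state in advance a rule for pooling I and II if stage I is sparse.
- Enter both factors crossed with time, or use an equivalent change-score model, since main effects alone leave the change contrasts unchanged.
- Apply the same rule to Aims 1–3.

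The cost is one sentence and a few degrees of freedom. The sample size does not change, because the stated power assumes no adjustment.

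### Sex and H&Y, read as main-effect covariates, cancel from the 3- and 16-month change contrasts, so adjusting for the stratification factors does essentially nothing there; minor, fixed by covariate-by-visit terms

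*Protocol article*

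**What the plan says.** In the Protocol article, Analyses, Aim 1, the primary outcome gets a "mixed effect model (treating subject as random) with between-subjects effect of group (PDAE vs. WALK) and within-subjects timepoints". The full list of time terms is "within-subjects timepoints (study entry, 3-month follow-up, 16-month follow-up) plus their interaction term", so study entry is one of three outcome rows and not a covariate. After a significant interaction, "we will test differences between PDAE and WALK in the change from baseline to 3 months and from baseline to 16 months" under Holm's procedure.

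On adjustment there is one sentence: "We will consider covariates sex and H&Y staging", with H&Y split into below III and III or above. It gives the grouping of H&Y but no covariate-by-time term.

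Both variables are randomization factors. Under Overall Study Design: "Participants will be stratified by sex and Hoehn & Yahr (H&Y) staging (I, II, or III").

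For Aim 2, "The secondary outcome Corsi Blocks Score will be analyzed using a similar mixed effects model". Aim 3 is likewise described as similar, with two timepoints. Neither aim names covariates.

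**The concern.** A trial that stratifies on sex and H&Y would normally want its analysis to use them, because stratified allocation removes their contribution from the arm difference and the standard error should reflect that. In this model the quantity of interest is a difference in change. A covariate that is constant over time and enters only as a main effect acts on a participant's overall level and not on change. The model could then be described as adjusted for sex and stage while the reported comparisons are the unadjusted ones. If sex or stage is related to change in MDS-UPDRS-IV, the available precision goes unused.

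**Working it through.** **1. The plan's own power figure.** Inputs from Power and Sample Size: d = 0.7 on change from baseline, 41 completers per group, alpha 0.025 and 0.05. Two-sided testing is assumed, since sidedness is not stated. A two-sample t-test has noncentrality 0.7 × √(41/2) = 3.17 on 80 df. Power is 81.0% and 87.9%. The article says "giving us 81 and 88% power for the comparisons at alpha level of 0.025 and 0.05, respectively", so the figures are reproduced, and without any covariate adjustment.

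**2. Why main effects cancel.** For participant *i* at visit *j*, with arm *g* and covariates *x* (sex, H&Y):

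y_ij = μ_j + γ_j·g_i + β·x_i + b_i + e_ij

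Change from baseline is y_ij − y_i0 = (μ_j − μ_0) + (γ_j − γ_0)·g_i + (e_ij − e_i0). The term β·x_i has gone. What remains on participants' overall level has its own free group coefficient (γ_0), so it carries no information on γ_j − γ_0. This holds for two-level or three-level H&Y.

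**3. Numerical check, complete data.** The article gives no variances or covariate effects, so these are assumed. There are 82 participants and three visits.

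- Random-intercept REML, one example: the contrasts are −0.3452 (SE 0.3840) at 3 months and −0.1240 (SE 0.3840) at 16 months. They are the same to four decimals with no covariates and with sex + H&Y main effects.
- Over 120 simulated data sets in each of three scenarios, the contrast estimates never differed between those two models.
- Generalized least squares with a fixed covariance, both compound-symmetric and unstructured, gave contrasts and SEs identical to eight decimals with and without the main effects. Only covariate-by-visit terms changed them. The cancellation does not depend on the random-intercept choice.

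**4. Dropout.** About 25% were made missing at 16 months, and the available data were analysed by likelihood. The 3-month estimate is unchanged. The 16-month estimate moves by 0.02 to 0.04 on average and by at most 0.16, against an SE of about 0.45 to 0.48. Within any completed, imputed data set the cancellation is again exact.

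**5. When by-visit terms would help.** Mean SE of the contrast, complete data:

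| Assumed relation of sex/H&Y to change | Main effects only | By-visit terms | Difference |
|---|---|---|---|
| none | 0.4053 | 0.4098 | 1.1% larger |
| moderate | 0.4111 | 0.4098 | 0.3% smaller |
| strong | 0.4285 | 0.4098 | 4.4% smaller |

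These simulations did not stratify allocation. The 1.1% penalty comes mainly from chance imbalance, which stratification would reduce.

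**6. Range for the unknown share.** Let *f* be the share of the variance of change explained by sex and H&Y (assumed; not in the article). The unadjusted SE is too large by 1/√(1 − f). Effective adjustment replaces d by 0.7/√(1 − f). Under stratified allocation the planned unadjusted test already benefits a little: its critical value *c* is in effect c/√(1 − f) against noncentrality 3.17/√(1 − f). All values use 80 df.

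| f | SE too large by | True error at nominal 0.05 | Power at 0.025, planned | Power at 0.025, adjusted |
|---|---|---|---|---|
| 0 | 0% | 0.050 | 81.0% | 81.0% |
| 5% | 2.6% | 0.044 | 81.6% | 83.1% |
| 10% | 5.4% | 0.039 | 82.2% | 85.2% |
| 15% | 8.5% | 0.034 | 82.9% | 87.3% |

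The gain is about 1.5, 3 and 4.4 points.

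**The case against.** The strongest reply is that the article does not say main effects only. It says the covariates will be considered, and the exact parameterisation is commonly left to a full protocol or analysis plan that is not shown. This stands in part: the form is open, and the point rests on the ordinary reading. But the article does list its model terms, names one interaction and even fixes the H&Y cut-point. Followed as written, the adjustment is inert for the tested comparison, which goes beyond an omitted detail.

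Several stronger readings are tempting and are not supported:

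- A reader might infer that the standard errors are too large. That holds only if sex or H&Y predicts change, on which the article gives nothing. With no such relation, by-visit terms give a slightly larger SE.
- A reader might infer that the results are strictly unchanged. That is exact for complete or fully imputed data. The plan assumes 25% attrition and refers to all available data together with multiple imputation, so under a pure likelihood fit it is only approximate at 16 months.
- A reader might infer that the tests are invalid or the power overstated. Neither follows. Any error in the SE is conservative, and the power calculation claims no covariate gain.
- A reader might extend the point outright to Aims 2 and 3. Their models are called similar, but no covariates are named for them.

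**Conclusion.** The point holds as a minor one. If sex and H&Y enter as main effects, the planned adjustment for the trial's own stratification factors leaves the 3- and 16-month comparisons exactly or very nearly as they would be without it. There is no bias and no inflated type I error, and the 81% and 88% power stands. The loss is conditional: an SE about 3% to 8% too large and roughly 1.5 to 4.4 points of power at alpha 0.025 if the factors explain 5% to 15% of the variance of change, and none if they explain nothing. The conclusion rests on the main-effects reading, on two-sided testing and on an assumed range for the explained share. A secondary reason to settle it is labelling: contrasts from such a model should not be presented as adjusted for sex and stage. The article does not say that they will be.

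**What to change.** State in the Aim 1 model that sex and H&Y enter together with their interactions with visit (sex × visit and H&Y × visit), and that the group-by-visit contrasts at 3 and 16 months are taken from that model. Fix this in advance, and replace the wording about considering covariates. Do the same in Aims 2 and 3 if the covariates are to be used there.

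The cost is one sentence of analysis text and two to three degrees of freedom per visit (one for sex, one or two for H&Y depending on its grouping). The SE would be very slightly larger if the factors do not predict change. No new data or participants are needed.
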